## Abstract

**Background:**

Critically ill patients frequently develop acute kidney injury that necessitates renal replacement therapy (RRT). At some centers, critically ill patients who are hemodynamically unstable and require RRT are treated with slow low-efficiency dialysis (SLED). Unfortunately, hypotension is a frequent complication that occurs during SLED treatments and may limit the recovery of kidney function. Hypotension may also limit the amount of fluid that can be removed by ultrafiltration with SLED. Fluid overload can be exacerbated as a consequence, and fluid overload is associated with increased mortality.

Occasionally, intravenous albumin fluid is given to prevent or treat low blood pressure during SLED. The intent of doing so is to increase the colloid oncotic pressure in the circulation to draw in extravascular fluid, increase the blood pressure, and enable more aggressive fluid removal with ultrafiltration. Nonetheless, there is little evidence to support this practice and theoretical reasons why it may not be especially effective at augmenting fluid removal in critically ill patients. At the same time, albumin fluid is expensive.

As such, we present a protocol for a study to assess the feasibility of a randomized controlled trial evaluating the use of albumin fluid versus saline in critically ill patients receiving SLED.

**Methods:**

This study is a single-center, double-blind, and randomized controlled pilot trial with two parallel arms. It involves randomly assigning patients receiving SLED treatment in the ICU to receive either albumin (25%) boluses or normal saline fluid boluses (placebo) to prevent and treat low blood pressure.

**Discussion:**

The results of this pilot trial will help with planning a larger trial comparing the efficacy of the interventions in achieving fluid removal in critically ill patients with AKI on SLED. They will establish whether enough participants would participate in a larger study and accept the study procedures.

**Trial registration:**

This trial is registered on ClinicalTrials.gov Identifier NCT03665311, registered on September 11, 2018.

**Electronic supplementary material:**

The online version of this article (10.1186/s40814-019-0460-3) contains supplementary material, which is available to authorized users.

## Background

The incidence of acute kidney injury (AKI) treated with renal replacement therapy (RRT) in the ICU has more than quadrupled over the last two decades [1–3]. Given the diversity of acute and chronic co-morbidities in patients with RRT-requiring AKI [2], pharmacologic interventions are likely to remain elusive [4]. Nonetheless, efforts to optimize the administration of RRT hold promise for reducing mortality and maximizing the likelihood of renal recovery [5].

The clinical response to hemodynamic instability during slow low-efficiency dialysis (SLED) (or any form of RRT) is often to give intravenous fluid boluses (including albumin (25%)), reduce the ultrafiltration rate, or stop treatment altogether [6, 7]. All of these interventions lead to a more positive net fluid balance in patients with RRT-requiring AKI who usually have minimal urine output. It is unclear if giving fluids in this situation (often with the view to allow further ultrafiltration later on during the same treatment) is beneficial given that (a) simply reducing the ultrafiltration rate alone may lead to adequate time for vascular refilling from the extravascular compartment to improve hemodynamics [6–8] and (b) hemodynamic instability may be unrelated to ultrafiltration/preload reduction [9–11]. This is important given mounting evidence that greater fluid overload in this context is an independent risk factor for increased mortality and longer term dialysis dependence [12–18].

Our recent systematic review found that no studies have previously assessed the efficacy of giving albumin to prevent hypotension or augment fluid removal during SLED [19]. Albumin is frequently used during SLED treatment, and there is lack of data to suggest that albumin is more effective for potentiating fluid removal during SLED as compared with normal saline.

The primary aim of this pilot trial is to determine if, for critically ill patients treated with SLED for AKI, randomization to receive albumin (25%) boluses versus normal saline placebo boluses is feasible, with respect to the recruitment rate, blinding, and adherence to the protocol.

## Methods

### Study design and setting

The study design is a single-center, parallel design, double-blind, and randomized controlled trial comparing albumin boluses to normal saline boluses during SLED treatments. This study will take place in the mixed medical-surgical intensive care units of a large tertiary care hospital in Canada.

### Study population and timeline

The research coordinators will screen daily for patients that are in ICU to determine whether or not a patient is eligible for this pilot trial. This screening includes review of patient charts and discussion with nurses and physicians from the Circle of Care. The ICU is a closed unit in the sense that it is the same team recruiting for all studies in the unit. This pilot trial will require 24 months to complete. The participant recruitment and follow-up will take place during month 7 to 21 included as Table 1.

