### Outcome measures

#### Feasibility

Recruitment rate, adherence to intervention, and completeness of follow-up are the principal outcome measures. This study aims to establish that (a) the team can randomize 30 patients into this trial over the study period and (b) trial participants have > 90% adherence to receiving albumin (25%) or normal saline placebo boluses during SLED treatments, as assigned through randomization. For this outcome, each SLED treatment (rather than patient) will be the unit of analysis.

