### Efficacy

Efficacy measures are to be assessed in an exploratory manner only. Efficacy outcomes will not be used to determine whether a subsequent, larger trial to assess efficacy outcomes is warranted. They will primarily be collected in order to identify any challenges with respect to data collection itself. Efficacy outcomes to be assessed by this pilot trial include (a) the “overall fluid removal” (i.e., percentage of target ultrafiltration achieved, calculated as the actual ultrafiltration volume divided by the target (ordered) ultrafiltration volume), (b) hemodynamic stability (i.e., initiation or increase in vasopressor dose(s) at the end of treatment, onset of MAP < 55 mmHg during treatment, absolute drop in MAP of ≥ 20 mmHg), (c) hospital length of stay, (d) ICU length of stay, (e) death at 1 year, and (f) dialysis dependence at 1 year. Efficacy measures (a) and (b) will be assessed at the level of SLED treatments while (c), (d), (e), and (f) will be analyzed at the patient level.

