### Sample size and analytic plan

A total of 30 patients with AKI requiring treatment with SLED (by definition, Kidney Disease Improving Global Outcomes (KDIGO) stage 3 AKI) will be recruited and followed up for this study over the period of 7–14 months at the Ottawa Hospital’s intensive care unit. As this is a pilot study, we do not include a formal sample size calculation. We felt that including 15 patients in each group would inform us about the practical aspects of conducting a larger RCT with respect to study procedures, recruitment, and data collection. Of particular note, this includes determining the average number of SLED sessions received per patient (which will inform the analysis plan for efficacy outcomes for a larger study).

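### The stated recruitment and follow-up windows are too short for every patient to reach the 1-year death and dialysis outcomes, and the loss falls on late-enrolled survivors

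*Protocol article*

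**What the plan says.** Three sections of the protocol article bear on this.

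- **Study population and timeline** sets the total length ("This pilot trial will require 24 months to complete") and one joint window for two activities: "The participant recruitment and follow-up will take place during month 7 to 21". It gives no separate date for the end of recruitment.
- **Outcome measures, Efficacy** ends its list of outcomes with "e) death at 1 year, and (f) dialysis dependence at 1 year", both analysed per patient. It also limits their role: "Efficacy measures are to be assessed in an exploratory manner only".
- **Sample size and analytic plan** says of the 30 patients that they "will be recruited and followed up for this study over the period of 7–14 months". This could mean calendar months 7 to 14 or a duration of 7 to 14 months. Neither clearly matches months 7 to 21.

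In addition, **Outcome measures, Feasibility** states: "Recruitment rate, adherence to intervention, and completeness of follow-up are the principal outcome measures". It attaches no time point or threshold to completeness of follow-up.

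**The concern.** An outcome at 1 year needs 12 months of observation after randomisation, unless the patient dies first. A joint window of 14 or 15 months for recruitment and follow-up leaves only two or three months in which a patient can be randomised and still reach 1 year before the window closes. No text shown provides for collecting status after month 21.

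Two things are at stake. First, the article collects efficacy outcomes mainly to expose problems with data collection. Status at 1 year, long after the ICU stay, would be tested only in early enrollees, and closure by calendar date would be mixed with true loss to follow-up. Second, the missing data are selective: an early death is known, whereas a late-enrolled survivor is undetermined. The analysis section plans proportions for dichotomous outcomes, and a proportion among patients with known status would overstate 1-year mortality.

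**Working it through.** **Inputs from the article.** Total length 24 months; joint window months 7 to 21; second statement 7–14 months; outcome horizon 12 months; 30 patients; assumed consent rate 20% (Limitations). The article states no number of patients expected to complete 1 year, so there is no figure to reproduce.

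**Assumption.** Accrual is uniform, because the article gives no accrual pattern.

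**Formula.** Let s be the start of accrual, E its end and F the end of follow-up, in months. The latest useful randomisation date is F − 12, so

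share with 12 months of potential follow-up = (F − 12 − s) / (E − s), bounded by 0 and 1.

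Month 7 is taken as s = 6 (counting months inclusively, so months 7 to 21 are 15 months) or s = 7 (by subtraction, 14 months).

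| Reading | s = 6 | s = 7 | Of 30 patients |
|---|---|---|---|
| Accrual to month 21, closure month 21 | 3/15 = 20% | 2/14 = 14% | about 4–6 |
| Accrual to month 21, closure month 24 | 6/15 = 40% | 5/14 = 36% | about 11–12 |
| Accrual months 7–14, closure month 21 | 3/8 = 38% | 2/7 = 29% | about 9–11 |
| Accrual months 7–14, closure month 24 | 6/8 = 75% | 5/7 = 71% | about 21–22 |

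If 7–14 months is instead the total duration of recruitment plus follow-up, the share is 0 for 7 months and (14 − 12)/14 = 14% for 14 months. If both activities end at calendar month 14, it is 0, since 14 − 12 = 2 falls before recruitment starts.

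**Could front-loaded accrual rescue the plan?** For all 30 patients to complete by month 21, they must enter within 2–3 months: 30/3 = 10 to 30/2 = 15 per month. Spread over the window, the rate is 30/15 = 2 to 30/14 = 2.1 per month. At 20% consent, 30 patients imply 30/0.20 = 150 eligible patients; within 3 months that is 50 per month.

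**Known death status.** Let m be the share who die before closure among patients who cannot complete 12 months. The article gives no mortality figure, so m is an assumption. In the narrowest joint-window case (s = 6, closure month 21), death status is known for 6 + 24m patients, which passes 15 once m exceeds 9/24 = 37.5%. With closure at month 24 it is 12 + 18m, passing 15 once m exceeds 3/18 = 16.7%. For m of 30–60% this gives about 13–20 and 17–23 patients.

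**Direction of bias.** Let q be the true 1-year mortality, with m no larger than q. For closure at month 21, the expected proportion dead among those with known status is roughly (6q + 24m)/(6 + 24m). It equals q only when m = 0 and rises with m. At the limit m = q (every 1-year death falls before closure), q = 30% gives (1.8 + 7.2)/(6 + 7.2) = 9/13.2 = 68%, and q = 60% gives (3.6 + 14.4)/(6 + 14.4) = 18/20.4 = 88%. These are upper limits under assumed mortality, shown for direction and possible size.

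**The case against.** The best defence has four parts.

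1. **No recruitment end date is stated.** A joint window may mean that recruitment stops well before month 21. With accrual in months 7–14 and closure at month 24, 71–75% have a full year. This stands: a reader might infer that the outcomes cannot be observed for most patients, but the documents do not establish that. Still, the favourable reading needs follow-up beyond the stated month 21 and leaves about a quarter of patients short.
2. **Early deaths count.** A patient who dies before closure has a known death outcome, and these are severely ill patients. This stands too, so the table describes potential follow-up, not the number with known death status. It does not help late-enrolled survivors, and it is what makes the missing data selective.
3. **Completeness of follow-up need not fail.** A reader might infer that this principal feasibility outcome must fail by design. The article does not tie it to 1 year and sets no threshold; its two numerical aims concern 30 randomised patients and adherence. That inference is unsupported.
4. **Little depends on these outcomes.** They are exploratory, the article says efficacy will not decide whether a larger trial goes ahead, and the progression criteria concern recruitment, enrolment share and complications. This limits severity.

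Table 1 is not visible and could list assessment points. However, the text ties it to the same month 7 to 21 window.

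**Conclusion.** The timeline and sample size sections conflict with the 1-year outcomes, and with each other. Under uniform accrual, the share with 12 months of potential follow-up ranges from 14–20% to 71–75% across the four calendar readings in the table, and is lower still if 7–14 months is a total duration. No reading gives all patients a full year unless accrual is strongly front-loaded. In late-enrolled survivors, 1-year dialysis dependence would be unobserved, and 1-year mortality among patients with known status would be biased upward by an amount that depends on mortality the article does not state.

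Severity is moderate. The recruitment, adherence and progression decisions are unaffected, so a reading that the pilot's feasibility conclusions are undermined goes beyond the text.

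**What to change.** Reconcile the three sections by stating separate end dates for recruitment and for follow-up. Then take one of two routes.

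- **Keep 1 year.** End the 1-year follow-up at last randomisation plus 12 months: about month 21 + 12 = 33 if recruitment runs to month 21, or 14 + 12 = 26 if it ends at month 14. Obtain vital and dialysis status by chart review or telephone. Report feasibility on the current schedule and the 1-year outcomes later.
- **Keep 24 months.** Replace the 1-year horizon by a shorter one that fits the stated follow-up window. With follow-up ending at month 21, the horizon can be at most 21 minus the month of last randomisation, so recruitment must stop before month 21.

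In either case, compute completeness at the chosen horizon against patients due at that time point, so that calendar closure is not counted as loss to follow-up.

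The cost is a change of timeline wording and, on the first route, status checks on at most 30 patients. The downside is later reporting of two exploratory outcomes, or a shorter horizon for them.

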**Table 1 Tab1:**
[figure not shown]
Study period content for the schedule of enrollment, interventions, and assessments for the SAFER-SLED pilot trial

Recommended content can be displayed using various schematic formats. See SPIRIT 2013 Explanation and Elaboration for examples from protocols

**List specific timepoints in this row

#### Inclusion criteria

≤ 18 years oldAdmission under the care of ICU and AKI treated with SLED (stage 3 AKI per Kidney Disease Improving Global Outcomes (KDIGO) AKI guidelines)

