### Ethical issues and trial registration

The pilot trial will be conducted in accordance with Health Canada’s Good Clinical Practice guidelines, the current Declaration of Helsinki, and the Tri-Council Policy State: Ethical Conduct for Research Involving Humans. The patients in this study are often not competent enough to consent to research due to their illness; many are intubated or are on respirator. Given this, we will have to seek consent for their participation from their designated substitute decision maker. Patients’ family who agree to participate in this study will provide a written informed consent by the research coordinator, included as Additional file 1. If during anytime of the study the patient regains competency, they will be provided with information, as is presented in the pamphlet included as Additional file 2, but will not be required to formally consent unless the intervention is ongoing (i.e., they are still receiving SLED). In most cases, patients are very unlikely to regain competency while still receiving SLED as it is only used as RRT when there is hemodynamic instability and patients tend to be severely ill and intubated. Patients can withdraw from the study at any time. Any data that were collected will then be discarded, destroyed, and not used in the study. All patients will be informed that they can withdraw from the study at any time. The study protocol, informed consent forms, and information pamphlet have been approved by the Ottawa Health Science Network Research Ethics Board. The trial is registered at the US National Institutes of Health (ClinicalTrials.gov) # NCT03665311.

Access to medical records and study data will be limited to authorized personnel listed on the study delegation log or permitted by the study agreement. Access to electronic data will be password protected and auditable, electronic data will be stored on a hospital network with firewall and security back-up measure in place, and paper copies of the study data will be stored securely in locked cabinets and in locked offices.

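### The age criterion as printed admits only patients aged 18 or younger, contradicting the population that the rest of the protocol describes

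*Protocol article*

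**What the plan says.** The first inclusion criterion, run together with the second in the available text, is "≤ 18 years oldAdmission under the care of ICU and AKI treated with SLED". No other section of the article states an age limit or modifies this one.

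The surrounding sections describe the population as follows:

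- **Aim (Background):** the question is whether, "for critically ill patients treated with SLED for AKI, randomization to receive albumin (25%) boluses versus normal saline placebo boluses is feasible". No age is given.
- **Setting (Study design and setting):** the "mixed medical-surgical intensive care units of a large tertiary care hospital in Canada".
- **Consent (Ethical issues and trial registration):** "The patients in this study are often not competent enough to consent to research due to their illness", so "we will have to seek consent for their participation from their designated substitute decision maker". Later, "If during anytime of the study the patient regains competency, they will be provided with information", and formal consent is required from a patient who recovers capacity while the intervention is still running.

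Eligibility then feeds two outputs. The Feasibility part of the analytic plan reports the proportion of eligible SLED patients who are randomized, and also the proportion not eligible. The Progression criteria require more than 25 recruits and enrolment of 15% of all eligible patients.

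**The concern.** An upper age limit of 18 describes a trial in children and adolescents. Nothing else in the article does. If research staff applied the criterion as printed, every SLED patient aged 19 or over would be logged as not eligible, and the pilot would measure feasibility in a different and probably very small group.

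If staff disregarded it and enrolled adults, each participant aged 19 or over would fail a stated inclusion criterion. The published protocol would then not document the population studied.

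In both cases the recruitment proportion and the 15% progression threshold rest on a denominator that the article defines wrongly. Those two figures are central to the decision on a larger trial.

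**Working it through.** There is no sample-size or power figure to reproduce. The article says "As this is a pilot study, we do not include a formal sample size calculation". The check is mainly a comparison of sections, followed by simple arithmetic on the denominator.

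**Step 1. Is the sign a text-reading fault?** This is unlikely. The Efficacy outcomes contain "absolute drop in MAP of ≥ 20 mmHg" with the sign pointing the expected way. The strict signs in the outcome sections (adherence > 90%, MAP < 55 mmHg) also print correctly.

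**Step 2. Does the criterion fit the other sections?**

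| Section | What it implies | Fits an upper limit of 18? |
|---|---|---|
| Ethical issues: reason for incapacity | Illness, not being a minor | No |
| Ethical issues: who consents | Designated substitute decision maker; no parental consent or assent | No |
| Ethical issues: recovery | Patient can consent personally once competent | No |
| Study design and setting | General medical-surgical ICUs; no paediatric unit named | Poorly |
| Background, aim | Critically ill SLED patients; no age stated | Neutral |

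The consent process is the strongest evidence and the setting is supporting evidence. A patient aged exactly 18 qualifies whichever way the sign points.

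**Step 3. What does the denominator have to supply?** The inputs are a target of 30 participants (Sample size and analytic plan), an assumed consent rate of 20% (Limitations), and progression thresholds of more than 25 recruits and 15% of eligible patients (Progression criteria).

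- Eligible patients needed for 30 participants: 30 / 0.20 = **150**.
- Eligible patients needed for 26 participants, the smallest number above 25: 26 / 0.20 = **130**.

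Both assume that every eligible patient is approached, so they are minimums. They do not depend on the direction of the sign. They show only how many patients the age rule must let through.

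**Step 4. What would the printed rule do?** Let *f* be the share of otherwise eligible SLED patients aged 18 or younger. The article does not give *f*, so the values below are assumptions. Take 150 otherwise eligible patients:

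- eligible under the printed rule = 150 × *f*
- expected participants = 150 × *f* × 0.20 = 30 × *f*
- apparent recruitment proportion if 30 patients of any age are enrolled but the denominator follows the printed rule = 30 / (150 × *f*)

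| Assumed *f* | Eligible as printed | Expected participants | 30 enrolled / eligible as printed |
|---|---|---|---|
| 5% | 7.5 | 1.5 | 400% |
| 10% | 15 | 3 | 200% |
| 50% | 75 | 15 | 40% |
| 100% | 150 | 30 | 20% |

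To reach 26 participants from this pool under the printed rule, *f* would have to be at least 26/30 = 87%. The last column shows that enrolling patients of any age while counting eligibility by the printed rule gives a meaningless proportion: it exceeds 100% whenever *f* is below 20%.

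**The case against.** The best reply is that this is a one-character slip in a journal article and not a design decision. Coordinators screen daily by chart review and discussion with the clinical team, and an ethics board approved the full protocol and consent forms. None of the operational documents are shown and they may well carry the right sign. On that view, an empty eligible pool or near-universal protocol deviation is hypothetical. The trial is also single-center with one recruiting team, so different sites cannot apply the rule differently.

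Much of this stands. A slip is the most plausible cause, and whether the working forms share it cannot be known from the article. It is also true that the word adult never appears, that the aim states no age, and that the intended population is inferred. Some supporting details are weak: a pregnancy exclusion is compatible with adolescents, and the fixed bolus volumes and blood-pressure cut-offs are not tied to age in the document. The figure of 150 is context and does not measure the error.

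None of this removes the contradiction. The criterion is the operative eligibility rule in the public protocol, and no other section overrides it. A reader, auditor or planner of the larger trial cannot tell from the article which rule produced the eligible count. Nor is this a detail lost in condensation: the article states the rule, and states it in a way that its own consent section contradicts.

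**Conclusion.** The concern holds and must be fixed. As printed, the age criterion excludes everyone aged 19 or over and cannot be reconciled with the consent process or, less decisively, with the setting. A reversed inequality is the most likely explanation.

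The established consequence is that the eligible denominator behind the recruitment proportion and the 15% progression threshold is wrongly defined on paper. The numerical effect on recruitment cannot be computed because no age distribution is given. That very few patients aged 18 or younger receive SLED in these ICUs is an assumption, although a plausible one. With 150 otherwise eligible patients and 20% consent, the printed rule would miss the target of more than 25 recruits unless at least 87% of them were 18 or younger. Whether any patient would actually be wrongly screened depends on forms that are not shown.

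**What to change.** - The sponsor should confirm the intended age limit against the ethics-approved protocol and correct the inclusion criterion, presumably to ≥ 18 years, with a published correction to the article.
- Check that the screening log and eligibility form carry the confirmed limit, and amend them only if they do not.
- State that the recruitment proportion, the not-eligible proportion and the 15% progression criterion all use the corrected rule. If any patients were screened under the printed sign, reclassify them before these figures are calculated.

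The cost is a one-character correction and a short check of the forms. The sample size, randomization and analysis methods do not change.
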